### Sample Size, Power, and Analysis Plan

Assuming a 15% noncompletion, we plan to enroll 106 participants in the trial to ensure 90 participants complete the study. With 90 participants (45 in each group), we will have 80% power to detect a significant difference in the change in mean daily step count from baseline to 12 weeks between the treatment and control groups for a moderate standardized effect size (Cohen *d*=0.60) using a two-sided significance level of .05.

For Aim 1, we will analyze the efficacy of the ExerciseRx platform using a linear mixed effects model with average daily step count each week as our outcome, fixed effects for week, treatment assignment, and the week-treatment interaction, and a random intercept for each participant. The presence of a significant interaction will indicate that the change in step count over the 12-week study period is impacted by treatment assignment. If differences in demographic or other clinically relevant characteristics between the two groups are found in the descriptive analysis, sensitivity analyses will be conducted, including those characteristics as adjustment variables in the model. Post hoc analyses will include independent and paired sample 2-tailed *t* tests to determine if there are differences between treatment groups at specific time intervals or differences between specific time intervals within a treatment group.

Similar models will be used for Aim 2 and for the secondary physical activity outcomes (activity volume and proportion meeting physical activity guidelines), using each of the secondary outcome measures as the outcome variable in the linear mixed-effects model. As no correction for multiple comparisons will be implemented for these analyses, any significant findings will be considered as hypothesis-generating.

For the qualitative analysis, the interview transcripts will be coded using Dedoose software. Two trained qualitative analysts will independently analyze the data using reflexive thematic analysis, a well-established method for interpreting qualitative data [53]. This approach emphasizes the researchers’ active role in identifying patterns across the data and involves intentional engagement with subjectivity and reflexivity throughout the analytic process. In conducting our analysis, we will draw upon our diverse backgrounds in design, health informatics, patient care, and clinical research to interpret the data and generate themes, while remaining attentive to how participants’ experiences and attitudes may differ from our initial assumptions.

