## Methods

### Design

To address Aims 1 and 2, we are conducting a two-group parallel (1:1) assessor-masked randomized controlled trial designed to compare the ExerciseRx platform to usual care. We will use qualitative research methods to explore implementation factors (Aim 3). Outcomes are being collected at baseline, post a 12-week treatment period (primary end point), and at a 3-month follow-up after the treatment period. We selected a 3-month follow-up because it is feasible in a 3-year study and sufficient time to see a change in activity behavior. We preregistered the trial at ClinicalTrials.gov (NCT06270641) on February 21, 2024, before enrolling the first participant. Figure 3 provides the study design and participant flow.

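### The primary mixed model names only a random intercept, so its week-by-treatment test can exceed 5% false positives if weekly steps are serially correlated or participants trend differently

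*Protocol article*

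**What the plan says.** Under Sample Size, Power, and Analysis Plan, the Aim 1 outcome is the average daily step count for each week. The model has "fixed effects for week, treatment assignment, and the week-treatment interaction, and a random intercept for each participant". The decision rule follows: "The presence of a significant interaction will indicate that the change in step count over the 12-week study period is impacted by treatment assignment". No random slope, residual correlation structure or robust standard error is named, and the text does not say whether week is a linear term or a set of categories. The only sensitivity analysis described adds covariates if the arms differ on baseline characteristics.

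The Primary Outcome section provides for a baseline week and 12 intervention weeks. A participant therefore contributes 13 values if the baseline week is an outcome row and 12 if it is not; the model text does not settle this.

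The power statement concerns a different quantity, the "difference in the change in mean daily step count from baseline to 12 weeks between the treatment and control groups", tested "using a two-sided significance level of .05". It reads "With 90 participants (45 in each group), we will have 80% power", at a Cohen d of 0.60.

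**The concern.** With independent residuals, a random intercept makes every pair of weeks equally correlated and gives all participants in an arm the same underlying trend. The interaction is a within-person contrast over time, so the random intercept cancels out of it and protects it against nothing. If adjacent weeks resemble each other more than distant ones, or if people drift up or down at their own rates, the model counts the weekly deviations as more independent information about the trend than they hold. The standard error is then too small and the confidence interval too narrow.

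The article gives reasons to expect both features. The same phone records passively every week. Relapses and falls are followed through the study. The Study Limitations section anticipates variation in step data across participants and plans to explore phone-carrying patterns. At stake is the trial's primary efficacy test: the article labels only the secondary findings hypothesis-generating, so a significant interaction would be read as evidence that the app works.

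**Working it through.** **Inputs from the article.** Two-sided alpha .05; 45 completers per arm; 1:1 allocation; d = 0.60; 15% noncompletion; 106 enrolled; 12 or 13 weekly values; random intercept only.

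**Assumed, because the article gives no figure.** AR(1) correlation of a participant's weekly residuals from 0 to 0.7; standard deviation (SD) of personal slopes from 0 to 0.15 residual SD per week, so that 12 weeks of drift has an SD of 0 to 12 × 0.15 = 1.8 residual SD.

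**Step 1. The plan's own figure.** Noncentrality = 0.60 × √(45/2) = 2.846. The normal approximation gives Φ(2.846 − 1.960) = 81.2%, and the noncentral t with 88 df gives 80.4%. Enrolment is 90/0.85 = 105.9, rounded up to 106. Both figures reproduce, for a comparison of two-time-point change scores.

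**Step 2. Variance ratio, linear week, 13 values.** With complete data the random-intercept test equals a pooled within-person test. Let w be the centred weeks (−6 to 6), so S = Σw² = 182. Let R be the true residual correlation matrix, and take the residual variance as 1.
- True variance of one person's slope: w′Rw/S².
- Variance the model assumes: s²/S, where s² averages (13 − ΣR/13)/12 and ΣR is the sum of all entries of R.
- At correlation 0.5, w′Rw/S = 2.12 and s² = 0.859, so the ratio is 2.12/0.859 = 2.47. At 0.3 and 0.7 it is 1.69 and 3.76.
- For independent residuals and slope variance equal to k times the sampling variance of one person's slope, the ratio is (1 + k)/(1 + k/12) with variation in both arms. At k = 1 this is 2/1.083 = 1.85. With variation in the treated arm only it is (1 + k/2)/(1 + k/24); at k = 1 this is 1.5/1.042 = 1.44.

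The actual type I error is about 2 × [1 − Φ(1.96/√ratio)]. Ratios of 1.69, 2.47 and 3.76 give critical values of 1.51, 1.25 and 1.01, hence about 13%, 21% and 31%. Ratios of 1.85 and 1.44 give about 15% and 10%.

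**Step 3. Simulation under no treatment effect** (4,000 trials per scenario, 45 per arm, 13 weekly values, complete data):

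| Assumed truth | Week linear | Week categorical (12 df) |
|---|---|---|
| Independent, common slope | 4.6% | 4.8% |
| AR(1) 0.2 | 9.7% | 6.0% |
| AR(1) 0.3 | 13.3% | 6.0% |
| AR(1) 0.5 | 21.8% | 7.3% |
| AR(1) 0.7 | 30.8% | 9.5% |
| Slope SD 0.02 / 0.05 / 0.10 / 0.15 | 6.0 / 10.3 / 20.7 / 32.1% | 5.2% to 8.3% |
| AR(1) 0.3 and slope SD 0.05 | 18.1% | not tabulated |

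With 12 weekly values the ranges are 5.1% to 30.0% (linear) and 4.5% to 10.0% (categorical). Repeat simulations put the upper end of the categorical global test near 11%. A t test on each participant's own fitted slope, which allows for both features, stays at 4.6% to 5.6% in every scenario.

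**Step 4. Supportive check with dropout** (REML fits, 106 enrolled, 15% dropout, linear week). The random-intercept model gave 3.2% under independence, 8.8% with slope SD 0.05, 18.4% with slope SD 0.10 and 19.2% with AR(1) 0.5. Adding a random slope at slope SD 0.10 brought the error to about 4%. These runs are few (120 to 250 per scenario) and many fits gave convergence warnings, so the conclusion rests on Steps 2 and 3.

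**The case against.** The strongest reply has four parts.

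- **Nothing in the article quantifies the correlation.** With neither serial correlation nor differing slopes the test is at its nominal level. This stands, and every inflated figure above is conditional.
- **The large figures need week to be linear.** The article does not say so. The planned post hoc t tests at specific time intervals, and a power statement framed as baseline-to-week-12 change, fit categorical week at least as well. This also stands; under that reading the excess is roughly 0 to 6 percentage points.
- **The app's individualised progression might seem to guarantee differing slopes in the treated arm.** A reader might infer this, but what the app individualises is the weekly goal (3%, 2% or no increase), not the steps taken. If the app affects nobody, the goals create no slope variation. Personal trends under that null need another source, such as health, season or phone carrying. That is plausible but undocumented. If slopes vary in the treated arm only, the k = 1 figure falls from about 15% to about 10%.
- **The residual covariance may be settled in an unseen analysis plan.** An article need not give it, and its absence alone is no finding. But the article does state the random effects and the decision rule, and a plan that follows that sentence with default residuals and standard errors inherits the problem.

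**Conclusion.** The point holds conditionally. As written, the primary model offers the interaction test no protection against serial correlation or person-specific trends. Fitted with independent residuals and model-based standard errors, its type I error is about 10% to 30% for linear week and about 5% to 11% for categorical week, under assumed AR(1) correlations of 0.2 to 0.7 or modest slope variance. It is 5% if neither feature is present.

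Two stronger readings are not supported. One is that false positives are known to run far above 5%: that needs both a correlation the article does not report and a linear week it does not state. The other is that the sample size is wrong: 80% power and 106 enrolled both reproduce, although for a two-time-point change rather than for the weekly interaction.

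**What to change.** State whether week enters as linear or categorical and whether the baseline week is an outcome row, and replace the random-intercept-only specification.

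- **Linear week:** add a participant random slope for week and/or use participant-clustered robust standard errors with a small-sample correction.
- **Categorical week:** use a structured serial residual covariance, or robust standard errors.

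A fully unstructured covariance is not needed. With 13 weekly values it would have 13 × 14/2 = 91 parameters for about 90 completers.

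The cost is a sentence or two in the analysis plan, slightly more analysis work and a somewhat wider confidence interval. For example, at AR(1) 0.3 with linear week the correct standard error is √1.69 = 1.30 times the one the random-intercept model reports. No further data or patients are needed. The article places the start of data analysis in January 2026 and states that the statistician is masked to allocation, so the change can be made before analysis starts without knowledge of the results.

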### Assessment Procedures and Measures

#### Overview

All participants complete baseline and outcome assessments using REDCap, a web-based data capture platform [28] that can be completed by any digital device with internet access. It includes a human verification service (reCAPTCHA) to avoid responses from bots. Outcome assessments are collected at baseline, post a 12-week treatment period (primary end point), and at a 3-month follow-up after the treatment period. We obtain step count data from all participants throughout the trial and collect data from all randomized participants, regardless of their adherence to treatment (ie, intent-to-treat). Participants receive up to US $150 remuneration for completing the REDCap assessments (US $50 for each assessment point).

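### The post hoc t tests on step count, within arms and between arms at unnamed time points, should give way to one named week-12 contrast from the primary mixed model

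*Protocol article*

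**What the plan says.** All the relevant text is in the Protocol article, mainly under Sample Size, Power, and Analysis Plan.

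- **Primary analysis.** A linear mixed model of weekly average daily steps has fixed effects for week, arm and their interaction, and a random intercept per participant. A significant interaction is the stated sign that treatment affects the change in steps.
- **Follow-up on the same outcome.** Independent and paired two-tailed t tests, labelled post hoc, are to look for "differences between treatment groups at specific time intervals or differences between specific time intervals within a treatment group". The text does not say which intervals or how many, whether the between-arm tests use step levels or changes from baseline, or whether the tests depend on a significant interaction.
- **Multiplicity.** The only statement closes the next paragraph, on Aim 2 and the secondary activity outcomes: "As no correction for multiple comparisons will be implemented for these analyses, any significant findings will be considered as hypothesis-generating".
- **Sample size.** It targets the between-arm difference in change: "we will have 80% power to detect a significant difference in the change in mean daily step count from baseline to 12 weeks", for a "moderate standardized effect size (Cohen *d*=0.60") and "using a two-sided significance level of .05". The Design section makes the end of the 12-week treatment period the primary end point.

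**The concern.** A paired t test inside one arm asks whether that arm changed. It does not ask whether the app did anything. A change shared by both arms is plausible here: both receive the guideline review and the same materials, and both are told to carry the phone, which itself affects how many steps are recorded. With a shared change, one arm can cross the significance threshold and the other miss it by chance alone, and the result can be misread as an app effect.

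The between-arm t tests are randomised comparisons, but their number is open and they carry no correction. The sentence calling results hypothesis-generating most naturally belongs to the secondary outcomes, so these tests on the primary outcome have no clear exploratory status beyond the words post hoc.

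Finally, the quantity that sized the trial, the between-arm difference in change from baseline to week 12, is not named as a contrast to be reported from the model. The only named test that compares the arms at a single time point is the independent t test, whose scale is not fixed. At stake are the secondary statements about when, and in which arm, steps rose.

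**Working it through.** **1. The plan's own figure.** Inputs from the Sample Size section: "With 90 participants (45 in each group"), d = 0.60 on change, two-sided 0.05, 15% noncompletion. Noncentral t power for a two-sample test with 45 per arm and d = 0.60 is 0.804 (0.812 by normal approximation). Enrolment: 90 / (1 − 0.15) = 105.9, so 106. The stated 80% power and 106 participants reproduce.

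**2. Within-arm paired tests.** Assume an equal true change m in both arms, in SDs of change, so the true between-arm difference is zero. With n = 45, the chance of a significant increase in one arm is p = P(T > t(0.975; 44)), where T is noncentral t with 44 degrees of freedom and noncentrality m√45. The arms are independent, so the chance that the app arm is significant and usual care is not is p(1 − p).

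| m (assumed) | p | p(1 − p) |
|---|---|---|
| 0 | 0.025 | 0.024 |
| 0.1 | 0.096 | 0.087 |
| 0.2 | 0.259 | 0.192 |
| 0.3 | 0.503 | 0.250 |
| 0.4 | 0.747 | 0.189 |
| 0.5 | 0.907 | 0.085 |

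The value 0.25 is the mathematical maximum of p(1 − p).

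**3. Between-arm tests at several time points.** This is a simulation of two-sample t tests at 0.05 with 45 per arm, no effect, and an equal correlation r between time points (assumed). It gives the chance of at least one false positive. The twelve-test figures moved by about 0.01 or less between simulation runs.

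| r | 2 tests | 12 tests |
|---|---|---|
| 0.6 | 0.09 | 0.27 to 0.28 |
| 0.7 | 0.08 | 0.23 |
| 0.8 | 0.08 | 0.18 to 0.19 |
| 0.9 | 0.07 | 0.13 |

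**4. Power at week 12, if the independent t test uses unadjusted levels.** Let ρ be the correlation between baseline and week 12 (assumed), with equal variances. The SD of change is √(2(1 − ρ)) level SDs, so d = 0.60 on change is δ = 0.60√(2(1 − ρ)) level SDs. A test of levels has effect size δ. A baseline-adjusted contrast has effect size δ/√(1 − ρ²). A test of change keeps 0.60.

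For ρ = 0.7: δ = 0.60 × √0.6 = 0.465; adjusted, 0.465/√0.51 = 0.651.

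| ρ | Levels | Change | Baseline-adjusted |
|---|---|---|---|
| 0.5 | 0.80 | 0.80 | 0.90 |
| 0.6 | 0.71 | 0.80 | 0.88 |
| 0.7 | 0.59 | 0.80 | 0.86 |
| 0.8 | 0.43 | 0.80 | 0.84 |
| 0.9 | 0.24 | 0.80 | 0.82 |

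The test of levels falls behind the test of change only when ρ exceeds 0.5.

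**The case against.** The strongest reply is that none of this decides efficacy. Aim 1 has one decision rule, a between-arm interaction, and the t tests are called post hoc. No sentence lets a within-arm change support a claim of benefit. If a between-arm t test on change stands in for the interaction, the pattern of a significant app arm and a non-significant control arm coincides with a significant between-arm result in at most about 2.5% of trials with no true difference. This stands, and it limits the point to the follow-up analyses.

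Four stronger readings are tempting, and the document does not support them.

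- **That the t tests are the only route to a week-12 difference.** The mixed model yields it. With week as a category and baseline as reference, it is the week-12 interaction coefficient; with week linear, it is the interaction slope times the elapsed weeks. The contrast is unnamed, not unavailable.
- **That twelve weekly tests are planned.** The number of intervals is not given. With assessments at baseline, 12 weeks and a 3-month follow-up, two post-baseline comparisons are just as natural a reading.
- **That the week-12 comparison is made with a weak test.** This needs both unadjusted levels and a correlation above 0.5, and the article fixes neither. A t test on change keeps the planned 80%.
- **That available-case t tests breach intent-to-treat.** The statement under Assessment Procedures and Measures is a commitment to "collect data from all randomized participants, regardless of their adherence to treatment (ie, intent-to-treat"). It concerns data collection, and a post hoc test on those observed does not contradict it.

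It can also be said that the number and scale of post hoc tests belong in a statistical analysis plan that is not shown. That is fair for those details. It does not cover the choice that the article does state, which is within-arm and time-point t tests on the primary outcome when a mixed model is already planned.

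**Conclusion.** The point holds as a cheap improvement to the follow-up analyses. The primary test and the sample size are sound on this point.

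The paired tests do not address the treatment effect. A misleading contrast between the two within-arm results arises in about 2% to 25% of trials with no true difference, depending on an assumed shared change of 0 to 0.5 SD. The uncorrected between-arm tests carry a chance of at least one false positive of about 7% to 9% for two time points and 13% to 28% for twelve, for assumed correlations of 0.6 to 0.9. The loss of power is conditional: 0.59 at ρ = 0.7 and 0.43 at ρ = 0.8 if levels are compared, against 0.80 on change and about 0.84 to 0.86 with baseline adjustment. The shared change, both correlations and the number of time points are assumptions; the document gives none of them.

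**What to change.** In the analysis plan, before unmasking:

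1. Replace the post hoc t tests with between-arm contrasts from the primary mixed model, using all available data from randomised participants.
2. Name one key contrast: app minus usual care in change from baseline to week 12, with its 95% CI.
3. Report within-arm changes descriptively, with CIs and no p values.
4. Label contrasts at other time points hypothesis-generating, as the plan already does for the secondary outcomes.

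The cost is two or three sentences and no new data. The downside is fewer p values to report.

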**Figure 2 figure2:**
[figure not shown]
The ExerciseRx app example screenshots.

This paper describes the rationale, aims, and protocol for the ExerciseRx-MS Trial, a randomized controlled trial designed to answer whether the ExerciseRx platform improves physical activity and other common symptoms and functional outcomes in adults with MS who are insufficiently active. The first aim is to evaluate the efficacy of the ExerciseRx platform relative to usual care in increasing physical activity, measured by average daily step count (primary outcome), activity volume, and the proportion who meet exercise guidelines in adults with MS who are insufficiently active. We hypothesize that participants randomized to the ExerciseRx app group will show a greater increase in physical activity at 12 weeks, as measured by daily average step count (primary outcome) and by total metabolic equivalent minutes of activity per week (secondary outcome) relative to participants randomized to usual care. We also hypothesize that a higher proportion of participants in the ExerciseRx app group will increase their minutes per week of moderate to vigorous intensity aerobic activity at 12 weeks (secondary outcome), relative to usual care participants.

The second aim is to evaluate the efficacy of the ExerciseRx platform relative to usual care on secondary outcomes, specifically symptoms (fatigue intensity, pain intensity, sleep, and depressive symptoms) and patient-reported functional outcomes (physical functioning, fatigue interference, pain interference, falls, and social participation). We hypothesize that participants in the ExerciseRx platform group will show greater improvements in secondary outcomes at 12 weeks relative to usual care participants. Additional secondary analyses will test maintenance of any treatment effects at a 3-month follow-up. We will also explore moderators of immediate (post-12 weeks) and 3-month follow-up outcomes, including demographics, disease course, and baseline participant factors (including fatigue, pain, depression, activity level, BMI, exercise self-efficacy, and disability) to explore potential moderators of treatment effects that can be evaluated a priori in future effectiveness and mechanistic research.

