### Recruitment, Enrollment Procedures, and Eligibility Criteria

The primary recruitment sources are referrals from clinic providers (physiatrists, neurologists, nurse practitioners, nurses, and psychologists) and the research registry. The EHRs of patients who are potentially interested in and eligible for the study are prescreened by a research coordinator to confirm MS diagnosis [26,27]. The coordinator then meets with the potential participant by phone to complete a standardized eligibility safety screening to ascertain eligibility. Staff track the recruitment outcomes for everyone who is screened, including reasons for ineligibility or declination. Basic demographic and MS disease characteristics (MS duration, course, and date of diagnosis) are obtained for those considered eligible who decline to enroll; this deidentified information will be used to compare them to study participants to assess the sample’s generalizability. All consent procedures are via REDCap (Research Electronic Data Capture; Vanderbilt University), an open-source, secure, HIPAA-compliant web-based platform for data capture (including e-consent and outcome survey administration) [28].

Inclusion criteria are (1) provider-confirmed diagnosis of MS; (2) 18 years of age or older; (3) Patient Determined Disease Steps (PDDS) score <3, indicating the potential for some gait disability although typically ambulates without an assistive device; [29-31] (4) insufficiently active, defined as <150 minutes of moderate intensity physical activity per week per the US National Physical Activity Guidelines, assessed using the Physical Activity Vital Sign [26,27,32] during screening; and (5) use of an iPhone with software version iOS14+ or an Android phone with version 5+. Exclusion criteria are (1) recent (past 4 weeks) or planned surgery during the study period which may impact step counts; (2) MS relapse within the last 30 days; (3) plans during the study period which may impact a participant’s daily access to Wi-Fi, which could interfere with server uploads of mobile phone data; (4) >3 falls in the past 6 months; and (5) contraindication to exercise.

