#### Secondary Outcomes: Physical Activity

The International Physical Activity Questionnaire-Short Form, which is validated for MS [41,42], will be given to participants at baseline to assess frequency and intensity of physical activity at each assessment timepoint. Activity intensity and frequency will then be used to calculate total MET-minutes per week for participants in each condition. The Physical Activity Vital Sign (described above) will also be obtained at each timepoint to determine the percentage of participants in each group that progress their total minutes spent in moderate to vigorous intensity physical activity per week toward the current physical activity guidelines (of >150 min of moderate intensity or >75 min of vigorous activity per week).

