#### Secondary Outcomes: Symptoms and Function

The following patient measures, all validated in MS, are obtained at the three outcome timepoints to investigate the effects of the ExerciseRx platform on symptom severity: Patient-Reported Outcomes Measurement Information System (PROMIS) pain intensity (PROMIS Pain Intensity Short Form) [43,44], fatigue severity (PROMIS Fatigue Intensity Short-Form)[43,45], depressive symptom severity (PROMIS Depression Short-Form) [43,46], and sleep disturbance (PROMIS Sleep Disturbance Short Form) [43,47]. We will also assess functional outcomes, specifically physical functioning (PROMIS Physical Function 10a) [48], pain interference (PROMIS Pain Interference Short-Form) [43,44], fatigue interference (PROMIS Fatigue Impact Short Form) [43,45], social participation (PROMIS Satisfaction with Participation in Social Roles Short Form 8a) [43], and self-reported falls (during the 6 months prior to randomization and throughout the study period).

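### A linear mixed model with a week-by-treatment interaction is prescribed for a yes/no activity outcome and for falls, and the activity responder is worded in three incompatible ways

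*Protocol article*

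**What the plan says.** **Model.** In the protocol article, Sample Size, Power, and Analysis Plan, the Aim 1 model has "fixed effects for week, treatment assignment, and the week-treatment interaction, and a random intercept for each participant". The section then states: "Similar models will be used for Aim 2 and for the secondary physical activity outcomes (activity volume and proportion meeting physical activity guidelines"), and the sentence ends by "using each of the secondary outcome measures as the outcome variable in the linear mixed-effects model". No logistic, Poisson or negative binomial model is named anywhere in the article.

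**Activity responder.**
- The first aim in the Introduction and the analysis section speak of the proportion who meet the guideline. The analysis section lists "activity volume and proportion meeting physical activity guidelines".
- The hypothesis in the same Introduction paragraph is that "a higher proportion of participants in the ExerciseRx app group will increase their minutes per week of moderate to vigorous intensity aerobic activity".
- Secondary Outcomes: Physical Activity uses the Physical Activity Vital Sign to find the percentage who advance their minutes toward the guideline, given as "of >150 min of moderate intensity or >75 min of vigorous activity per week".

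**Entry rule.** Participants must be "insufficiently active, defined as <150 minutes of moderate intensity physical activity per week", measured at screening with the same instrument.

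**Falls.** Falls are listed among the Aim 2 functional outcomes and are collected as "self-reported falls (during the 6 months prior to randomization and throughout the study period"). More than 3 falls in the preceding 6 months is an exclusion.

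**The concern.** A linear mixed model with a random intercept and a single residual variance suits the PROMIS scores. It is a poor default for a 0/1 outcome that barely varies at baseline and for a small, skewed count with different look-back periods. This is a stated choice of model, not a detail left to a fuller plan, because the sentence names the proportion explicitly.

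The three responder wordings are different endpoints. A participant who goes from 20 to 40 minutes a week succeeds under the second and third and fails under the first. Two of the three do not exist at baseline, so the prescribed interaction has nothing to estimate for them. At stake are the meaning of the responder result, the calibration of its test, and the interpretation and power of the falls comparison.

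**Working it through.** **1. The plan's own figure.** With 45 per arm, d = 0.60 and two-sided 0.05, the normal approximation gives 81.2% power and the noncentral t gives 80.4%. Enrolment is 90 / (1 − 0.15) = 105.9, so 106. Both agree with the article, and nothing below alters them.

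**2. Which responder can enter the stated model?**

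| Wording | Where | Value at baseline | Interaction estimable? |
|---|---|---|---|
| Meets guideline | First aim; analysis section | close to 0% | yes, but variance is unequal |
| Increases minutes | Hypothesis | none (needs two visits) | no |
| Advances toward guideline | Secondary outcomes | none (needs two visits) | no |

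Baseline is close to 0%, not exactly 0%. The entry rule concerns moderate minutes, while the success rule also accepts more than 75 vigorous minutes, so someone could enter already meeting it.

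**3. Effect of the near-zero baseline on the test.** Assume 0% at baseline, responder rate p at both later visits in both arms, variance v = p(1 − p), correlation ρ between the two later 0/1 values, visit as a category and complete data.

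*Three visits fitted jointly.* The expected within-person mean square is [2v − 3·(2v + 2ρv)/9] / 2 = v(2 − ρ)/3. The model therefore takes the variance of one person's change to week 12 as 2v(2 − ρ)/3. The true value is v. The ratio of model to true variance is (4 − 2ρ)/3, and the type I error is about 2[1 − Φ(1.96·√ratio)].

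| ρ | Ratio | Type I error (formula) | Simulated, 25% responders |
|---|---|---|---|
| 0.2 | 1.2 | 3.2% | 3.3–3.5% |
| 0.5 | 1.0 | 5.0% | 5.0–5.5% |
| 0.8 | 0.8 | 8.0% | 8.0–8.6% |

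Simulations with p from 10% to 40% give the same picture. One set placed correlations of 0.5 and 0.8 on an underlying continuous scale and found 3.0% to 6.0%. This is consistent, since those values correspond to ρ of only about 0.25 to 0.33 and 0.51 to 0.59 for the 0/1 outcome.

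*Baseline and week 12 only.* The within-person mean square is v/2, the model variance of the change is 2·v/2 = v, and the ratio is 1. Simulated type I error is 5.1% to 5.5%.

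**4. Falls.** The article gives no fall rates, so this is a single assumed scenario: gamma-Poisson counts with shape 0.7, mean 0.6 per 3 months before the entry cap, at most 3 falls in the 6 months before baseline, later windows of about 3 months, 45 per arm, true rate ratio 0.4.
- With no treatment effect, the mean raw count drops from 0.73 at baseline to 0.45 at the next visit in both arms, mostly because the window halves.
- Power at week 12: stated linear mixed model 28–30%; robust Poisson with baseline falls as covariate 55–57%; linear regression with baseline falls as covariate and robust standard errors 54–55%.
- Type I error is about 5% to 6% for all three.

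The two baseline-adjusted analyses perform alike, so the gain comes from using baseline falls as a covariate instead of differencing against them.

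**The case against.** Several points on the other side stand.

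- **The test need not be miscalibrated.** The Introduction treats the 3-month maintenance analyses as additional, so a model with baseline and week 12 only is a fair reading, and there the error is near nominal. A reader might infer that the guideline test is invalid whatever is fitted; the documents do not support that.
- **A linear model for a 0/1 outcome estimates a risk difference,** which is a useful quantity. The result would be poorly specified, not meaningless.
- **The falls windows are partly inferred.** The article states the 6-month look-back and collection over the study period, but no recall window per visit and no explicit statement that raw counts are analysed. Falls over the whole 26 weeks would match the baseline window. However, the Aim 2 hypothesis is set at 12 weeks, so an analysis by visit is likely.
- **The falls power loss is not caused by linearity.** A reader might infer that treating counts linearly halves power; the baseline-adjusted linear regression shows otherwise.
- **Entry below 150 and success above 150 minutes is not a contradiction.** The two do not overlap, and the success rule repeats the guideline as the Introduction gives it.
- **The aim and the analysis section agree on meeting the guideline,** so it would go too far to say that the endpoint is left to be picked after the data are seen.

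The words about similar models do not remove the problem, because the same sentence ends by naming the linear model. Hypothesis-generating status excuses the lack of multiplicity correction. It does not excuse an endpoint with three wordings or a comparison of counts over unequal exposure.

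**Conclusion.** Wrong as written, with moderate consequences. Three things follow from the text alone: a yes/no outcome is assigned to a linear mixed model; the responder has three wordings, two of which cannot enter the stated interaction; and the remaining one is near constant at baseline, so a single residual variance cannot hold.

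The sizes are conditional. Type I error of about 3% to 8.5% applies only to a joint three-visit fit, with assumed correlations of 0.2 to 0.8 and responder rates of 10% to 40%. The falls contrast of about 30% against about 55% rests on one assumed scenario and reflects baseline adjustment. The exposure problem arises only if falls are analysed by visit.

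The outcomes concerned are secondary, uncorrected and declared hypothesis-generating. The primary outcome, the 80% power and the enrolment of 106 stand.

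**What to change.** - Keep the linear mixed model for the PROMIS scores.
- Reconcile the Introduction, Secondary Outcomes: Physical Activity and the analysis section to one responder definition at week 12, naming instrument and threshold. Meeting the guideline is the natural candidate, since the aim and the analysis section already use it.
- Analyse that responder with a binary-outcome model (for example logistic regression) adjusted for baseline activity minutes and sex, and report the marginal risk difference with its confidence interval. Treat any other responder version as descriptive.
- Analyse post-randomization falls with a negative binomial or robust Poisson model, with log exposure time as offset and baseline falls as covariate. State the period that each falls report covers.

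The cost is a change of analysis wording, best recorded before the data are analysed. The proposed models use baseline minutes, sex and falls, all of which are already collected, and the sample size does not change.
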